### Quality standards

#### Randomization and blinding

Randomization occurs after completion of baseline assessments. An independent randomization administrator will complete randomization at the individual level using a computer-generated random number sequence in blocks of 6 in 1:1 ratio and with concealed allocation using numbered envelopes. The nature of the intervention makes it impossible to blind study participants. Treatment group assignments will therefore be non-blinded, but outcome assessors will be blinded to allocation.

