**Methods:**

This open-label, parallel-arm, phase II randomised control trial will recruit cancer patient-caregiver dyads across a large health network. Previously used written vignettes will be converted to video vignettes using the recommended methodology. Participants will be ≥18 years and be able to complete questionnaires. Dyads will be randomised in a 1:1 ratio to a usual care (UC) or VDST group. The VDST group will watch a video of several patient-caregiver dyads communicating personal values across different cancer trajectory stages and will receive verbal and written ACP information. The UC group will receive verbal and written ACP information. Patient and caregiver data will be collected individually via an anonymous questionnaire developed for the study, pre and post the UC and VDST intervention.

Our primary outcome will be ACP completion rates. Secondarily, we will compare patient-caregiver (i) attitudes towards ACP, (ii) congruence in communication, and (iii) preparation for decision-making.

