## Methods / design

### Study design and setting

This is a prospective, RCT with two parallel groups receiving usual care (UC) or VDST intervention forms part of a research program of ACP in cancer developed in accordance with the Medical Research Council framework for developing complex interventions [29]. In this exploratory study, participants are enrolled in the study as dyads – a patient diagnosed with incurable cancer and a nominated caregiver. In this study, caregivers are defined as a relative, partner, or friend who has a significant relationship with the patient and provides them with social, psychological, and physical assistance [30].

The study will be conducted across three sites in a large not for profit health network Melbourne, Australia. ACP in the hospital is governed by legislation through a jurisdictional Medical Treatment Planning and Decision Act 2016 [31]. The Act establishes a single framework for medical treatment decision-making for people without decision-making capacity that ensures that people receive medical treatment consistent with their preferences and values. Standard forms under the Act allow for the appointment of a Medical Treatment Decision Maker (MTDM) and Support Person and completion of a Values and Instructional Directive (Table 1).

**Table 1 Tab1:** Components of an advance care plan/directive

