**Fig. 1 Fig1:**
[figure not shown]
Study procedure

Patients and caregivers will be consented individually by the research facilitator and will complete individual baseline pre-questionnaires (Supplementary file). Participants will then be randomised as dyads to either the UC or VDST arm. All participants will be advised that participation is voluntary, they may withdraw at any time, and that all information gathered will be treated in the strictest confidence. Patients and caregivers will also be advised that non-participation will not affect their care or their choice to complete an ACP.

Patients from both groups will be advised to discuss their completed ACP with their general practitioner or treating specialist to clarify any questions. The completed ACP will have to be signed, witnessed and returned with the post-questionnaire in a stamped return envelope. Participants will be advised to return the questionnaires even if they choose not to complete the ACP. Participants will receive two telephone call prompts at two-week intervals on completion of the intervention as a reminder to return the completed documents. Returned ACP’s will be scanned into the hospital’s electronic record system, and a copy returned to the patient.

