#### VDST group

Participants randomised to the VDST group will be shown the video on a mobile computer. The video will be viewed by patient-caregiver dyads simultaneously. Research facilitators will offer to discontinue the video at any point if it elicits distress. Following this, the participants will be provided with a verbal explanation of ACP and be provided with the hospital’s ACP document, and verbal and written guidelines on how to complete the document. Questions will be fielded, and finally, participants will be provided with patient and caregiver post-questionnaires to be completed individually and returned with the completed ACP in a stamped return envelope.

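### The randomisation section names the individual as the unit where the rest of the article randomises dyads, and its single block size of 6 lets a fully informed observer deduce up to about a quarter of assignments

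*Protocol article*

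**What the plan says.** **Unit.** Under Randomization and blinding, the article says: "An independent randomization administrator will complete randomization at the individual level using a computer-generated random number sequence in blocks of 6 in 1:1 ratio". Under Study procedures it says: "Participants will then be randomised as dyads to either the UC or VDST arm". The Methods paragraph of the abstract agrees with the latter: "Dyads will be randomised in a 1:1 ratio to a usual care (UC) or VDST group". Study design and setting enrols participants in pairs, Sample size and power counts dyads (86 evaluable, 112 recruited), and the VDST group section says: "The video will be viewed by patient-caregiver dyads simultaneously".

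**Allocation method.** The list is a "computer-generated random number sequence in blocks of 6 in 1:1 ratio". No variation in block size is mentioned. The same sentence provides for an independent administrator and "concealed allocation using numbered envelopes". Treatment is open to participants; outcome assessors are blinded. Clinicians screen for eligibility. A research facilitator then obtains consent and baseline questionnaires before randomisation, and facilitators are present when the video is shown.

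**The concern.** Two separate matters arise in one sentence.

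First, the section that should govern how the list is built names a unit that the rest of the design cannot use. Both members of each pair consent, complete questionnaires and count as participants, so the individual naturally reads as one person. A list built on that reading would place some patients and their caregivers in different arms, which joint viewing does not allow.

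Second, with one block size and open treatment, the end of a block can be worked out from what went before. The facilitator role both recruits and learns the assignment. Someone who foresees the next assignment could, even unintentionally, influence which dyad is scheduled next or how the consent conversation runs. The article's Limitations section says that some patients are ambivalent about advance care planning or reject it. Readiness to complete a plan therefore varies between dyads and bears directly on the primary outcome.

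**Working it through.** **1. Literal reading of the unit.** Suppose patient and caregiver take adjacent slots in a 1:1 block of 6. Once the first is assigned, 5 slots remain, of which 3 belong to the other arm. The chance that the pair is split is 3/5 = 60%.

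**2. The plan's own sample size.** Inputs from Sample size and power: 37% against 67%, two-sided 5%, power 80%. The mean proportion is 0.52. With pooled variance and no continuity correction:

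n per group = [1.96 × √(2 × 0.52 × 0.48) + 0.8416 × √(0.37 × 0.63 + 0.67 × 0.33)]² / 0.30² = (1.385 + 0.567)² / 0.09 ≈ 42.3, rounded up to 43.

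This reproduces 43 per group, 86 in total; power at 43 per group is 80.6%. The calculation treats each dyad as one independent binary outcome, which fits one plan per patient.

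**3. Assignments fully determined by earlier ones.** Inputs: block of 6, 3 per arm, 20 equally likely arrangements. An assignment is determined once one arm is used up.

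| Position | Chance determined | Chance best guess is right |
|---|---|---|
| 1 | 0 | 0.5 |
| 2 | 0 | 0.6 |
| 3 | 0 | 0.6 |
| 4 | 2/20 = 0.10 | 0.7 |
| 5 | 8/20 = 0.40 | 0.7 |
| 6 | 1.00 | 1.0 |
| Sum | 1.5 | 4.1 |

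- With m per arm, the expected number determined per block is 2m/(m + 1) = 6/4 = 1.5, so 1.5/6 = 25%.
- Best guess over a full block: 4.1/6 = 68.3%, against 50% by chance.
- For 112 dyads (18 full blocks plus 4): 18 × 1.5 + 0.10 = 27.1, or 24.2%. Best guess: (18 × 4.1 + 2.4)/112 = 76.2/112 = 68.0%.
- For 86 dyads (14 full blocks plus 2): 14 × 1.5 = 21.0, or 24.4%.
- If there were three separate site lists of 37, 37 and 38 (an assumption): 27.0 of 112, or 24.1%.

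**4. Partial view.** As an illustration, assume one list shared by three equal sites in random order, no pooling of information between sites, and block position known. An assignment is then certain locally only if all three uses of the exhausted arm were seen locally, a factor of (1/3)³ = 1/27. That gives 25%/27 ≈ 0.9%, about 1 of 112 dyads.

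**5. Randomly varying block sizes.** Simulated on one list of 112, for an observer who knows the possible sizes but not their order, with sizes equally likely (the mixes are assumptions):

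| Blocks | Certain assignments |
|---|---|
| Fixed 6 | 27.1 (24.2%) |
| 4 and 6 | about 6.2 (5.5%) |
| 4, 6 and 8 | about 2.5 (2.3%) |

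Varying the size removes certainty, not the average advantage of guessing. Someone who always guesses the arm that is behind needs no knowledge of block size. Such a person is right 17/6 times per block of 4 and 41/10 times per block of 6, so (2.83 + 4.10)/10 = 69.3% under the 4-and-6 mix, much as under fixed 6.

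**The case against.** **The unit is a wording slip.** Every operational section is dyadic, and the phrase may have meant only that sites or clusters are not randomised. That is plausible, and it is why the correction is small. But the article does not say so, and the slip sits in the section that specifies the list.

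**Concealment is specified.** This is true and counts in the plan's favour. Envelopes hide the next assignment; they do not stop someone deducing it from earlier ones when the block size is known.

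**The route to steering is narrow.** Clinicians screen before the facilitator meets the dyad, and consent and baseline questionnaires come before randomisation. Nothing says that the screening clinicians see past assignments or that recruiting staff were told the block size. This stands as a limit on the risk. Scheduling and the consent conversation remain, and the block size is printed in the article.

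**The quarter is a ceiling.** This also stands. It needs an observer who sees every earlier assignment on a list, and who sees what is not described.

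**Blocks of 6 are a common choice in a pilot.** Agreed. This part is an avoidable weakness with a cheap remedy, not an error.

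**Conclusion.** The contradiction over the unit is certain, and the passages must be reconciled. The predictability is real but modest. It is at most about 24–25% of assignments (about 27 of 112 dyads), with a best guess right 68% of the time. This assumes every block has size 6 and an observer who knows that size and sees every earlier assignment on a list. With a partial view it could be as low as about 1%, under the assumptions shown.

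A reader might infer more than the documents support:

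- *That the stated power is undermined.* It is not. The outcome is one plan per dyad, and 43 per group is reproduced with the dyad as the unit.
- *That allocation is unconcealed.* It is not. Treatment is open once assigned, but the article specifies "concealed allocation using numbered envelopes" and an independent administrator.
- *That a quarter of assignments will in fact be foreseen.* That is an upper bound, because the article does not describe how far staff share what they see.
- *That one list serves the three sites, or that stratifying by site is needed.* The article does not say whether there is one list or several. A condensed article may leave that detail to the full protocol. Separate site lists would not reduce predictability (24.1%) and would show local staff their whole sequence.

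**What to change.** 1. Under Randomization and blinding, replace the reference to the individual with: *at the dyad level, one allocation per patient-caregiver dyad*. This changes a few words and costs nothing.
2. For allocations not yet used, have the independent administrator generate the remaining list with block sizes drawn at random (for example 4 and 6), and do not disclose the sizes to recruiting staff. Keep the concealed envelopes. The cost is regenerating the unused list and a possible imbalance of a few dyads. The gain is the loss of certain foreknowledge (about 24% down to about 5.5% in the illustration), not of the average guessing advantage.
3. If the list is already used up, correct the wording and state in the trial report the block design and who knew the block size.

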## Background

All people have the right to make decisions about how they are cared for in the future. However, many lose this ability as they approach the end-of-life (EOL). Advance care planning (ACP) may provide an avenue to ascertain patients’ wishes in circumstances where they are unable to articulate them due to a loss of capacity [1, 2]. A recent multidisciplinary panel of ACP experts defined ACP “as a process that supports adults at any age or stage of health in understanding and sharing their personal values, life goals, and preferences regarding future medical care” [3]. Elucidating ACP enhances desirable EOL outcomes, including patient-caregiver confidence and satisfaction [4, 5], quality of death [2, 6], and family bereavement experiences [6]. ACP requires reflection and communication and is an iterative process that is both individualized and shared [7, 8]. Contemporary views have shifted from ACP focused solely on treatment decisions at the EOL and medically orientated advanced directives. It instead encourages conversations that communicate personal values and life goals to support patient-caregiver communication and decision-making [9], family preparation [10, 11], and the actualization of ACP’s through innovative interventions [12].

Specific ACP challenges are recognized in cancer care, with ACP in cancer limited in completion, scope, timing, and translation into desired care [13]. Patients commonly prefer discussions later in their cancer journey [14], initiated by their treating physicians, and prefer multiple opportunities for conversations [13, 15]. The physician is required to strike a balance between engendering hope and maintaining truthful communication that ideally incorporates prognostic information [16]. Low uptake may be associated with standardized programs failing to capture the complex social and emotional nuances experienced by the cancer patient and their family across ages, genders, cancer types, and trajectories [17].

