### Participants and recruitment

Patients with non-curable cancer will be recruited from the oncology and palliative care across different sites at the health network. Eligible patients will have a diagnosis of incurable cancer and not have completed current ACP documents. Patients who have previously only appointed a MEPOA will be eligible to participate. Both patients and caregivers will have to be over the age of 18, be sufficiently proficient in English, and have a clinically determined prognosis of a minimum of 8 weeks post-randomization. Patients and caregivers will be ineligible for the trial if they are deemed too unwell and are unable to give informed consent due to cognitive or language barriers.

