### Development of video vignettes

The video vignettes will be developed from the findings of our preliminary research into ACP in cancer patients [7, 10]. These studies incorporated the use of written vignettes, depicting a cancer patient’s scenarios across four stages of the cancer trajectory. In our preliminary studies, patients were depicted as declining in function and requiring various levels of care [7, 10, 32, 33]. Vignettes were presented to patients and caregivers in interviews and focus groups to elicit views on ACP and subsequently to patient-caregiver dyads as part of a facilitator-guided intervention in a feasibility study [32]. Qualitative secondary analysis on the use of written vignettes revealed that the vignettes provide a platform to promote values-based conversations and may facilitate congruence in communication between the patient and caregiver [33].

In developing the video vignettes, the research team will adhere to suggested guidelines for the preparation of scripted video vignettes which are 1) deciding on the appropriateness of the use of video vignettes, 2) developing a valid script, 3) designing valid manipulations, 4) converting written scripts to video, 5) administering the videos [34].

The written script will be developed by senior clinicians, drawing from cases used in previous studies [7, 10]. Manipulations will include representation of patient-caregiver dyads from differing ages, gender, stages of illness and relationships e.g. older patient and spouse/partner; middle-aged patient and sibling; younger patient and friends). This, as well as settings and furnishing, will be selected to enhance the participant’s perception of reality [34]. The video vignettes will depict dyads scenarios communicating across three stages of a cancer trajectory, with each stage introducing considerations for completion of different sections of an ACP (Table 2). Professional actors will be sourced from known professional college and university sources, and a pilot video will be created before the filming of the final videos. The video vignettes will be circulated to a multidisciplinary team for validation and approval and further editing before the final video intervention is created.

**Table 2 Tab2:** Predicted scenarios depicted in the video decision support tool

	Cancer stage	Values conversation depicted	ACP outcomes encouraged

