### Sample size and power

Based on the primary outcome of the completion of ACP documentation and assuming a completion rate of around 37% for the control group, with a total of 86 participants/dyads (43 per group) we will be able to show a significant improvement to 67% completion for the VDST group (power of 80%, two sided 5% significance level). Assuming an estimated dropout rate of 30%, recruitment of 112 dyads will be required. Based on previous published studies, we felt that a sample of this size would give us sufficient methodological experience to conduct a subsequent fully powered study [12].

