#### Data collected and measures used

Table 3 outlines the measures used at baseline and post-intervention. The baseline questionnaire will include the patient’s and caregiver’s demographic information, including age, sex, marital status, place of birth, the relationship between patient and caregiver, primary cancer diagnosis, and length of time living with the diagnosis. Patients will be asked if they had previously discussed prognosis with their doctor.

**Table 3 Tab3:** Measures used pre and post UC and VDST

Measures used	Patient		Caregiver	
	Baseline: Pre UC/VDST	Post UC/VDST	Baseline: Pre UC/VDST	Post-UC/VDST
Demographics	**×**		**×**	
DASS-21	**×**			
ACP Attitudes	**×**	**×**	**×**	**×**
CCAT	**×**	**×**	**×**	**×**
PDMS	**×**	**×**	**×**	**×**

*DASS-21* Depression, Anxiety and Stress Scale, *CCAT* Cancer Communication and Assessment Tool, *PDMS* Preparation for Decision Making Scale

The following variables and outcomes will be assessed:

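### Patients are pooled from oncology and palliative care without stratification, and no illness stage or recruiting service appears in the listed baseline data, so precision and the ability to adjust are given up

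*Protocol article*

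**What the plan says.** Recruitment (Participants and recruitment): "Patients with non-curable cancer will be recruited from the oncology and palliative care across different sites at the health network". All patients have incurable cancer. The section sets a minimum expected survival of 8 weeks after randomisation and no upper limit.

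Intervention (Development of video vignettes, with Table 2): the video covers three stages of illness, "with each stage introducing considerations for completion of different sections of an ACP". Table 2 pairs early diagnosis with appointing a decision maker and support person, progressive disease with the Values Directive, and approaching end of life with the Instructional Directive. Outcome assessment then examines completion of these same sections under the primary outcome.

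Allocation (Randomization and blinding): a "computer-generated random number sequence in blocks of 6 in 1:1 ratio and with concealed allocation using numbered envelopes". No stratification factor is named.

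Baseline data (Data collected and measures used, with Table 3): demographics, the relationship between patient and caregiver, "primary cancer diagnosis, and length of time living with the diagnosis", whether prognosis had been discussed, and DASS-21 for the patient. Stage, performance status and recruiting service are not listed. Statistical analysis plans an exploratory regression of ACP completion on socio-demographic and clinical variables.

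**The concern.** The two recruiting services are likely to see patients at different points of the illness, and the intervention is organised around those points. If completion differs between such patients, an unstratified trial of this size can end with arms that differ in case mix, and part of the observed difference in completion would then reflect that mix. With the listed data the analyst could neither show the imbalance nor adjust for it, except through partial proxies such as time since diagnosis. Time since diagnosis is a weak proxy, because a newly diagnosed patient may already have advanced disease.

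The article's stated purpose is to refine the tool and plan a multisite study. For that, the team would want to describe who completed which section by how ill they were. Later analysis cannot supply a variable that was not collected at entry.

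**Working it through.** **1. The plan's own sample size.** Inputs from Sample size and power: "assuming a completion rate of around 37% for the control group", "significant improvement to 67% completion for the VDST group", "power of 80%, two sided 5% significance level". With pooled variance and no continuity correction:

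n per arm = [1.960 × √(2 × 0.52 × 0.48) + 0.842 × √(0.37 × 0.63 + 0.67 × 0.33)]² / 0.30² = (1.385 + 0.567)² / 0.09 ≈ 42.3, so 43.

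The stated 43 per arm (86 dyads) reproduces, with 80.6% power. The design effect to keep in view is 30 points.

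**2. How often would the arms differ in case mix?** Assumption, not in the documents: a share q of patients comes from palliative care, and service stands in for stage as a two-level factor. Blocking on sequence does not balance this factor, so the SD of the difference in share between arms is √(2q(1 − q)/43).

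- q = 0.5: SD = √(0.5/43) = 0.108. A difference of at least 10 points arises in about 35% of trials, at least 15 points in about 16%, and at least 20 points in about 6–7%.
- q = 0.3: SD = 0.099. At least 10 points in about 31%, at least 20 points in about 4%.

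**3. What does that do to the result?** If completion differs by G between services, an imbalance d shifts the arm difference by G × d. With q = 0.5, the 95% range of the shift is ±1.96 × 0.108 × G. The share of outcome variance explained is q(1 − q)G² / (0.37 × 0.63). The documents give no value for G, so a range is shown, holding overall control completion at 37%.

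**4. What would a stratified analysis recover?** Simulation with 40,000 trials per setting, 43 per arm, q = 0.5 and a true effect of 30 points. It compares the unadjusted z-test with a Cochran-Mantel-Haenszel (CMH) test stratified by stage.

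| Gap G (points) | Completion, oncology / palliative | 95% shift (points) | Variance explained | Power, unadjusted | Power, CMH |
|---|---|---|---|---|---|
| 10 | 32% / 42% | ±2.1 | 1.1% | 80.0% | 80.4% |
| 20 | 27% / 47% | ±4.2 | 4.3% | 79.8% | 82.0% |
| 30 | 22% / 52% | ±6.3 | 9.7% | 79.8% | 84.2% |
| 40 | 17% / 57% | ±8.5 | 17.2% | 79.9% | 87.7% |

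Simulated binomial counts for gaps of 20, 30 and 40 points gave 4.2, 6.3 and 8.4, in agreement.

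**5. Is the unadjusted test still valid?** Yes. In the same simulation its type I error was 5.4–5.6% for gaps of 0 to 40 points, and already 5.4% with no stage effect at all. The mean estimated effect was 0.300 throughout. The CMH test ran at 4.9–5.1%, so its power advantage does not come from a looser test.

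The simulation did not stratify the allocation. The power gain in step 4 therefore comes from having the variable and using it in the analysis. Stratified allocation adds protection against a visible imbalance.

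**The case against.** The strongest reply has four parts.

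*Randomisation already does the work.* Both arms receive the ACP document and the same kind of verbal and written guidance, and chance imbalance is already part of the standard error. This stands. A reader might infer that the section results cannot be interpreted at all; the documents do not support that, because each section's comparison between arms is valid whatever the stage mix.

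*Table 2 does not assign sections to patients.* Every dyad in the video arm sees the whole video, so every section is encouraged in every viewer. Nothing in Tables 1 or 2 calls a section unsuitable at a given stage. This also stands. It rules out the tempting reading that a patient with good function who only appoints a decision maker has done all that the video asks and is then miscounted as a failure.

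*The protocol gives no stage effect on completion.* The Background says "Patients commonly prefer discussions later in their cancer journey". That concerns the preferred timing of discussions. It does not say that completion rises with stage, and it gives no rates. This stands, which is why the gap above is an assumption with a range. Because all patients are incurable, the spread of stage is also narrower than the video's, although function and closeness to death can still vary widely.

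*The article is condensed.* The questionnaire is a supplementary file, the full protocol is not shown, and recruiting service could probably be recovered from recruitment records. This stands in part. However, the article does state the allocation method and itemise the baseline data, and the variable around which the video is built is in neither. If the full protocol already collects it, the data-collection part of this point is met.

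**Conclusion.** The point holds as an inexpensive improvement. It is not a flaw that invalidates the trial. The allocation as described and the baseline data as listed leave illness stage and recruiting service unbalanced by design and unavailable for adjustment. The primary and section comparisons remain unbiased on average, with type I error unaffected.

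The size depends on assumptions that the documents do not supply: 43 evaluable dyads per arm, a 50% palliative share, and a completion gap of 20 to 40 points. Under these, chance imbalance moves the arm difference by up to about 4 to 8 points in 95% of trials, which is modest against the 30-point design effect. Stratified analysis lifts power from about 80% to about 82–88%. With a gap of only 10 points the gain is negligible. If service or recorded stage tracks completion less closely than assumed, the gain shrinks accordingly.

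It would go too far to say that an imbalance could not be corrected at all. The planned regression could use time since diagnosis and cancer type as partial proxies, but it would lack stage itself.

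**What to change.** 1. At screening, have the clinician record two items: recruiting service (oncology or palliative care), and disease extent with performance status. Clinicians already screen for eligibility, and prognosis is already a clinical judgement at that point.
2. Stratify the allocation list by recruiting service, using two envelope series in blocks of 6.
3. Prespecify service and stage or performance status as covariates in the comparison of ACP completion between arms.
4. Report section completion by stage as descriptive only. Three stages would leave about 43 / 3 ≈ 14 evaluable dyads per arm per stage, too few for inference.

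Cost: two extra screening items, a second envelope series with one more incomplete block at the end of recruitment, and the added covariates. No extra patients or visits are needed. The items must be collected at entry, since reconstructing stage afterwards would be unreliable.
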